More recently, in 2024, a randomized controlled trial [4] comparing EST and ESBD reported that the primary endpoint, use of mechanical lithotripsy, was significantly lower in the ESBD group (20.0% vs. 4.0%, *P* = 0.028), and procedure time was also significantly shorter (18.5 min vs. 17.0 min, *P* = 0.047). However, the trial was prematurely terminated due to poor enrollment and included only 100 participants (50 per group) instead of the planned 220, which limits the generalizability of its findings.

Given these promising but preliminary data, ESBD is expected to be a valuable technique for managing small CBDS; however, no prospective studies have yet adequately evaluated its safety and efficacy. Therefore, we designed this randomized controlled trial to determine whether ESBD provides superior outcomes compared with conventional EST and to assess its potential as a new standard approach for papillary treatment during endoscopic management of small CBDS. Previous studies have been limited by small sample sizes, single-center designs, and heterogeneous protocols. The present trial addresses these limitations through a larger sample size, multicenter participation, and standardized procedural protocols.

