### Objectives {7}

The objective of this study is to compare the efficacy and safety of ESBD and EST in patients undergoing endoscopic transpapillary removal for small CBDSs. The primary aim is to determine whether the incidence of procedure-related adverse events is significantly lower in the ESBD group. Additionally, secondary comparisons will be made regarding outcomes related to stone removal efficacy, such as the proportion of cases requiring mechanical lithotripsy and the overall procedure time. Details of the study outcomes are summarized in Table 1.

**Table 1 Tab1:** The primary and secondary endpoints in the MARBLE trial

Outcome	Measurement variable/definition	Analysis metric	Time point

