**Secondary endpoints**			
Type and severity of procedure-related AEs	Classified using ASGE lexicon; detailed criteria applied for bleeding and pancreatitis (see Notes)	Descriptive	Within 30 days from the procedure
Technical success rate	Completion of ESBD or EST according to protocol	Binary outcome	Day of procedure
Clinical success rate	Complete stone removal in a single session	Binary outcome	Day of procedure
Total procedure time	Time from cannulation to completion of stone removal	Continuous (minutes)	Day of procedure
Time required for stone removal	Time from end of ESBD or EST to completion of stone removal	Continuous (minutes)	Day of procedure
Proportion of cases requiring lithotripsy	Use of mechanical lithotripsy (excluding mechanical tools used without fragmentation), electrohydraulic lithotripsy, or laser lithotripsy	Incidence proportion	Day of procedure
Stone recurrence rate	Reappearance of bile duct stones post-removal	Incidence proportion	5-year follow-up
Time to stone recurrence	Days from successful stone removal to confirmed recurrence	Time-to-event	5-year follow-up
Biliary event rate	Any biliary event (e.g., stone recurrence, cholangitis, cholecystitis, liver abscess, biliary cancer)	Incidence proportion	5-year follow-up
Time to biliary event	Days from successful stone removal to occurrence of any biliary event	Time-to-event	5-year follow-up
**Notes on adverse event definitions** The definitions and severity grading of procedure-related adverse events will follow the ASGE lexicon [7]. Among these, bleeding and pancreatitis are the most anticipated adverse events in this study and represent key safety outcomes; therefore, more detailed criteria are specifically defined for these two events **-Bleeding:** *Intra-procedural bleeding*: requires hemostatic intervention (excluding preventive measures) *Post-procedural bleeding*: confirmed by endoscopy or imaging study such as computed tomography, or inferred from clinical findings such as hematemesis, melena, or a drop in hemoglobin level that cannot be explained by other causes **-Pancreatitis:** The diagnosis is established when at least two of the following three criteria are met: (1) acute abdominal pain and tenderness in the upper abdomen, (2) elevated levels of serum or urinary pancreatic enzymes, and (3) imaging findings indicative of acute pancreatitis [8]			

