## Statistical methods

### Statistical methods for primary and secondary outcomes {20a}

For the primary outcome, group comparisons of categorical variables will be performed using Pearson’s chi-square test or Fisher’s exact test, as appropriate. A two-sided *p*-value of less than 0.05 will be considered statistically significant.

For secondary outcomes, categorical variables will also be analyzed using Pearson’s chi-square test or Fisher’s exact test. Continuous variables will be compared using the *t*-test or the Mann–Whitney *U* test, depending on the distribution. Normality of continuous variables will be assessed using the Shapiro–Wilk test before applying the *t*-test. Time-to-event variables will be analyzed using the log-rank test, and survival curves will be constructed using Kaplan–Meier estimates. To examine factors associated with each event, multivariable analyses such as linear regression, logistic regression, and Cox proportional hazards models will be applied with covariate adjustment. For multiple subgroup analyses, Bonferroni correction will be applied to adjust the p-value threshold to control the family-wise error rate. If the proportion of missing data exceeds 10%, multiple imputation will be conducted as a sensitivity analysis in addition to the available-case analysis. A two-sided *p*-value < 0.05 will be considered statistically significant for all analyses. All analyses will be performed using R.

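### The two-sided 0.05 significance rule extends to nine tested secondary endpoints with no stated status or order, and recurrence and biliary events are each tested twice

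*Protocol article*

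**What the plan says.** All of this is in the protocol article.

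- **Primary.** Statistical methods for primary and secondary outcomes {20a} compares the procedure-related adverse event rate by chi-square or Fisher test, and a two-sided p-value "of less than 0.05 will be considered statistically significant".
- **Secondary tests.** The same section assigns tests by type of variable: "For secondary outcomes, categorical variables will also be analyzed using Pearson’s chi-square test or Fisher’s exact test"; t-test or Mann–Whitney for continuous variables; and "Time-to-event variables will be analyzed using the log-rank test".
- **Multiplicity.** One adjustment is stated: "For multiple subgroup analyses, Bonferroni correction will be applied to adjust the p-value threshold to control the family-wise error rate". Two sentences later, p below "0.05 will be considered statistically significant for all analyses".
- **Endpoints.** Table 1 lists ten secondary endpoints. Type and severity of adverse events is marked descriptive. The other nine have a binary, proportion, continuous or time-to-event metric. Recurrence and biliary events each appear twice, as a proportion and as a time; the latter is, for example, "Days from successful stone removal to occurrence of any biliary event". Stone recurrence is itself named as one kind of biliary event.
- **Role.** Objectives {7} makes the adverse event rate the primary aim and adds: "Additionally, secondary comparisons will be made regarding outcomes related to stone removal efficacy".
- **Timing.** Interim analyses {21b} says short-term and long-term outcomes are analysed separately under a predefined statistical analysis plan, which is not shown.

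**The concern.** Multiplicity among secondary endpoints is often left to the analysis plan, and silence in an article would be no finding. Here the article is not silent. It raises family-wise error, applies the control to subgroups only, and then fixes 0.05 as the threshold for every analysis. A later plan that ranked the secondaries or called them exploratory would have to depart from that published rule.

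The single primary endpoint concerns safety. Every conclusion about stone-removal efficacy (clearance, lithotripsy, procedure times, recurrence) must therefore come from the secondaries. As written, any of the nine that falls below 0.05 may be called statistically significant on the same terms as the primary.

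The paired long-term endpoints add a separate problem. If the proportion test and the log-rank test for the same event fall on opposite sides of 0.05, nothing stated says which result stands. Outcome assessors and analysts are unblinded (Who will be blinded {17a}), so these choices are better fixed in advance.

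**Working it through.** **1. Primary, for reference.** Inputs from Sample size {14}: 15.8% against 4.4%, two-sided 0.05, 80% power, 1:1, 10% loss. The two-proportion formula gives 109 per arm, or 126 with continuity correction; 126 / 0.9 = 140 per arm, 280 in total, as stated. There is one primary contrast at 0.05 and no interim analysis, so its type I error is not in question.

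**2. Count of tested secondaries (Table 1 with {20a}).**

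| Time point | Endpoints | Test | Number |
|---|---|---|---|
| Day of procedure | technical success, clinical success, lithotripsy | chi-square/Fisher | 3 |
| Day of procedure | total procedure time, stone-removal time | t / Mann–Whitney | 2 |
| 5 years | recurrence rate, biliary event rate | chi-square/Fisher | 2 |
| 5 years | time to recurrence, time to biliary event | log-rank | 2 |

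Total: 5 + 4 = 9. The article gives no family-wise figure for these, so there is none to reproduce.

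**3. Independent tests, no true difference on any endpoint.** Chance of at least one p < 0.05 = 1 − 0.95^k.

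- k = 9: 1 − 0.95^9 = 0.370
- k = 5 (short-term only): 1 − 0.95^5 = 0.226
- k = 4 (long-term only): 1 − 0.95^4 = 0.185

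**4. Correlated tests.** The article gives no correlations, so these are assumptions. With nine normal test statistics sharing a common correlation ρ, the chance is 1 − ∫ φ(u) [Φ((1.96 − √ρ·u)/√(1−ρ)) − Φ((−1.96 − √ρ·u)/√(1−ρ))]^9 du.

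| ρ | 0 | 0.3 | 0.5 | 0.7 | 0.9 |
|---|---|---|---|---|---|
| At least one of nine | 37.0% | 32.6% | 26.9% | 20.2% | 12.4% |

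A structured correlation is more realistic: high within the two procedure times and within each rate/time pair, lower elsewhere. Simulations of that kind gave 26% to 31%. Counting each duplicated long-term pair once (k = 7) gives 1 − 0.95^7 = 30.2% at ρ = 0 and 11.4% at ρ = 0.9.

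**5. The two threshold sentences.** The Bonferroni sentence lowers the threshold for subgroup tests. The closing sentence sets 0.05 for all analyses and makes no exception. Methods for additional analyses {20b} lists about twenty subgroup variables, so a reader needs to know which sentence governs.

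**The case against.** The case on the other side is substantial, and much of it stands.

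- **No family-wise promise.** The article claims family-wise control only for subgroups. Unadjusted per-test thresholds for endpoints labelled secondary, below a single primary, are common. This stands: 5% is a benchmark brought from outside, and the plan does not break a commitment.
- **One family or two.** Short-term and long-term outcomes are to be analysed separately, so treating all nine as one family is a choice. This stands, and it is why 22.6% and 18.5% are given beside 37.0%.
- **No single figure.** A reader might infer that nine tests at 0.05 imply a rate of about 27%. They do not: that figure needs a common correlation near 0.5 or some similar structure, which the article does not supply. Fisher's exact test is also conservative with sparse events, so actual rates may be lower.
- **The claim is tied to the primary.** A reader might infer that a secondary result could carry the trial if the primary fails, especially from the Background aim "to determine whether ESBD provides superior outcomes compared with conventional EST". The documents do not support that. Trial design {8} defines superiority by the adverse event rate, and the Discussion makes a new standard conditional on fewer procedure-related adverse events.
- **Bonferroni.** A specific rule normally overrides a general one, so the two sentences are better called ambiguous than contradictory.
- **The unseen plan.** It may give the secondaries a status and name the main long-term test. That disposes of any complaint about absence alone. It does not dispose of the stated all-analyses rule, which such a plan would have to contradict.

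**Conclusion.** The point holds as a flaw in a stated rule. The primary inference and the sample size are sound. What needs repair is a significance label granted to nine secondary tests on the same terms as the primary, and two long-term outcomes tested twice without precedence.

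The size is a range: 37.0% under independence, falling to about 12% at a common correlation of 0.9. It assumes no true difference on any of the nine and tests that run at exactly 0.05. Which value applies cannot be settled from the article, but every value shown is well above the 5% a reader may attach to a single significant result. The change is worth making because it is cheap and limits unsupported efficacy claims. It does not mean the trial's main conclusion is at risk.

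**What to change.** In {20a}:

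1. Restrict the two-sided p < 0.05 significance statement to the primary endpoint.
2. State that secondary endpoints are exploratory, reported as effect estimates with 95% confidence intervals, and that no superiority claim will rest on them.
3. Make the time-to-event analysis the single test for recurrence and for biliary events, and report the two proportions descriptively.
4. If the closing 0.05 sentence is kept in any general form, add to it: except subgroup analyses, which use the Bonferroni-adjusted threshold.

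A fixed testing sequence opened by a significant primary would be needed only if the sponsor wants a confirmatory efficacy claim; that is a matter of preference and not part of this point.

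The cost is a few sentences, carried into the analysis plan. No patients or data are added and the primary test is unchanged. The downside is that an isolated secondary p-value below 0.05 can no longer be reported as a significant finding. Recruitment is scheduled to run until 31 March 2027, so on that timetable the change can be made before enrolment closes.

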### Interim analyses {21b}

No interim analysis is planned for this study. Analyses of short-term and long-term outcomes will be conducted separately in accordance with the predefined statistical analysis plan.

### Methods for additional analyses (e.g., subgroup analyses) {20b}

Subgroup analyses will be conducted based on the following variables: sex, age, body mass index, performance status, comorbidities, presence of liver cirrhosis or renal failure, history of acute pancreatitis, use of antithrombotic agents (none, antiplatelet agents, anticoagulants), platelet count, PT-INR, presence of cholangitis, gallbladder, or gallstones, common bile duct diameter, size and number of bile duct stones, endoscopist’s ERCP experience (< 200 or  ≥ 200 procedures), presence of periampullary diverticulum, use of rectal NSAIDs, pancreatic duct guidewire placement, and placement of a pancreatic stent.

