### Intervention description {11a}

The procedure will be performed within 14 days of patient enrollment. A standard duodenoscope will be advanced into the duodenum, followed by biliary cannulation using a standard catheter and a 0.025–0.035-inch guidewire. A standard wire-guided sphincterotome will be used to perform EST. In the ESBD group, a minimal incision is made in the 11 to 12 o’clock direction without reaching the hooding fold. In the EST group, a medium incision extending beyond the hooding fold is performed. This standard will be reinforced through pre-study training and photographic documentation to ensure consistency among all operators. In the ESBD group, EPBD is subsequently performed with a diameter matching the lower bile duct (typically 6–10 mm). After completion of these procedures, stone removal will be performed using a retrieval basket and balloon catheter. Compared with conventional EST, ESBD is expected to reduce adverse event risk including bleeding.

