### Relevant concomitant care permitted or prohibited during the trial {11d}

Concomitant care and interventions are generally permitted at the discretion of the treating physician, provided they do not interfere with the study protocol. The use of antithrombotic agents will be managed according to the Guidelines [5, 6]. Antithrombotic agents may be withheld or adjusted as appropriate based on individual patient risk and in consultation with the prescribing physician.

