### Implementation {16c}

The computer-generated allocation sequence will be developed and managed by the UMIN INDICE system. Investigators at each participating center will be responsible for enrolling eligible participants. Once enrollment is completed, the system will automatically assign participants to either the ESBD or EST group according to the pre-programmed randomization algorithm.

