## Assignment of interventions: blinding

### Who will be blinded {17a}

This is an open-label trial; therefore, neither participants nor treating endoscopists will be blinded to group allocation. Outcome assessors and data analysts will also not be blinded due to the nature of the intervention. However, to minimize bias in outcome evaluation, procedure-related adverse events will be classified and graded according to predefined criteria based on the American Society for Gastrointestinal Endoscopy lexicon, and all relevant outcomes will be objectively assessed using standardized metrics.

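### Three planned subgroup variables (pancreatic stent, pancreatic duct guidewire and, probably, rectal NSAIDs) arise after open-label allocation, so comparisons within them are not protected by randomisation

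*Protocol article*

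**What the plan says.** Section {20b} of the protocol article introduces its list with "Subgroup analyses will be conducted based on the following variables". The list runs from sex and age to "use of rectal NSAIDs, pancreatic duct guidewire placement, and placement of a pancreatic stent". Baseline characteristics and procedural measures stand side by side, and no different handling is given for the latter.

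Other sections fix the order of events:

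- **Allocation, {16c}:** "Once enrollment is completed, the system will automatically assign participants to either the ESBD or EST group".
- **Procedure, {11a}:** "The procedure will be performed within 14 days of patient enrollment".
- **Blinding, {17a}:** "neither participants nor treating endoscopists will be blinded to group allocation".
- **Co-interventions, {11d}:** "Concomitant care and interventions are generally permitted at the discretion of the treating physician", provided they do not interfere with the protocol.

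Randomisation is stratified by pre-procedural drainage and antithrombotic use ({16a}), and by none of the three measures. For subgroups, section {20a} says that "Bonferroni correction will be applied to adjust the p-value threshold to control the family-wise error rate". It later says that a two-sided p-value below 0.05 "will be considered statistically significant for all analyses".

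**The concern.** A subgroup comparison keeps the benefit of randomisation when membership is settled before allocation. Membership of a stented or non-stented stratum is settled during the ERCP, by someone who knows the arm. If operators place stents more readily in one arm, the stented patients in the two arms are no longer alike in underlying risk. A difference between them then mixes the treatment with the selection.

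Pancreatitis is one of the two events that the article singles out as key safety outcomes, and it counts towards the primary endpoint. A published result that ESBD is, or is not, safe when a stent or an NSAID is used could be read as guidance for practice. The discussion section says that the trial is meant to inform clinical decisions and guidelines.

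**Working it through.** **1. The plan's own figure, and whether it is touched.** Inputs from {14}: 15.8% (EST), 4.4% (ESBD), two-sided α = 0.05, power 80%, 1:1 allocation, 10% loss. Mean rate 0.101, difference 0.114.

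- Uncorrected: n = [1.960·√(2·0.101·0.899) + 0.842·√(0.158·0.842 + 0.044·0.956)]² / 0.114² = 108.5, so 109 per arm.
- With continuity correction: n′ = (108.5/4)·[1 + √(1 + 4/(108.5·0.114))]² = 125.4, so 126 per arm.
- With 10% loss: 126/0.90 = 140 per arm, 280 in total.

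The stated 280 reproduces exactly with the continuity correction. No subgroup enters this calculation, so the point does not change it.

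**2. Order of events for each variable.**

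| Variable | When it arises | Strength of the concern |
|---|---|---|
| Pancreatic stent | During the ERCP, arm known | Strongest |
| Pancreatic duct guidewire | During the ERCP, arm known; probably at cannulation, which {11a} places before the papillary step | Weaker |
| Rectal NSAIDs | Not stated; peri-procedural use would follow allocation | Conditional on timing |

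**3. How large a spurious effect could be.** The article gives no usage rates by arm, so all inputs here are assumptions. Suppose that half the patients are high risk (adverse-event risk 16%) and half low risk (4%), and that neither the arm nor the stent affects the risk. The overall rate is 0.5·16 + 0.5·4 = 10%, close to the 10.1% mean of the planning rates. Within an arm, with stent probabilities s_H (high risk) and s_L (low risk):

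- Risk among stented = (0.5·s_H·0.16 + 0.5·s_L·0.04) / (0.5·s_H + 0.5·s_L)
- Risk among non-stented: the same, with 1 − s_H and 1 − s_L.

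| Scenario | EST s_H / s_L | ESBD s_H / s_L | Stented: EST, ESBD (difference) | Non-stented: EST, ESBD (difference) |
|---|---|---|---|---|
| Same use | 40% / 10% | 40% / 10% | 13.6%, 13.6% (0.0) | 8.8%, 8.8% (0.0) |
| Moderate | 40% / 10% | 45% / 20% | 13.6%, 12.3% (−1.3) | 8.8%, 8.9% (+0.1) |
| Larger | 40% / 5% | 50% / 35% | 14.7%, 11.1% (−3.6) | 8.6%, 9.2% (+0.6) |
| Extreme | 60% / 5% | 60% / 60% | 15.1%, 10.0% (−5.1) | 7.6%, 10.0% (+2.4) |

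Differences are ESBD minus EST in percentage points, from unrounded risks. The true effect is zero in every cell.

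**4. A second set of assumed inputs.** Suppose that 20% of patients are high risk (20%) and the rest have 7.5%. All high-risk patients are stented in both arms, and 15% of low-risk patients are also stented in the ESBD arm only.

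- Stented, EST: 20.0%.
- Stented, ESBD: (0.20·0.20 + 0.80·0.15·0.075)/(0.20 + 0.12) = 0.049/0.32 = 15.3%.
- Spurious difference: 4.7 points in favour of ESBD. The non-stented strata both show 7.5%.

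**5. Set against the noise.** With 140 per arm, the stented strata in step 4 hold 140·0.20 = 28 EST and 140·0.32 ≈ 45 ESBD patients. The standard error is √(0.20·0.80/28 + 0.153·0.847/45) = 0.093, or about 9 points. A shift of 4.7 points is about half a standard error.

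**6. Effect on the multiplicity threshold.** The list has 18 items as written, or 22 if joined items are split. Removing three moves the Bonferroni threshold from 0.05/18 = 0.0028 to 0.05/15 = 0.0033, or from 0.05/22 = 0.0023 to 0.05/19 = 0.0026.

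**The case against.** The strongest reply is that the bias is hypothetical. Nothing in the article says that operators will use these measures differently by arm, and with equal use the bias is zero. The motive is also open to doubt. The background section ties the higher pancreatitis risk to balloon dilation alone and hypothesises that adding a minimal incision lowers it. The retrospective rates that it cites are 2.6% (EST) and 1.9% (ESBD). A reader might infer that ESBD is the arm in which pancreatitis is feared, and that all three measures will be chosen accordingly. The article does not support that; it leaves the possibility open and does nothing to close it. The reply is also right that the strata are small and that a shift of this size would seldom pass a Bonferroni threshold. That limits false claims of significance. It does not make the reported estimates unbiased.

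Other, stronger readings should not be drawn:

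- **No interaction test is planned.** The article does not say which p-values Bonferroni applies to, and the form of the test may stand in the analysis plan, which is not shown.
- **Many tests at 0.05 make a false positive likely.** That describes a procedure the article does not plan, since Bonferroni is specified for subgroups.
- **The two significance rules contradict each other.** On an ordinary reading the specific subgroup rule governs subgroups; the general sentence is loose wording.
- **Pre-procedural drainage is wrongly left out.** No rule requires a stratification factor to be a subgroup, so this is a preference.
- **The 0.05 level should be kept for the primary endpoint only.** That would alter every secondary test, and nothing in the subgroup argument justifies it.

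**Conclusion.** The point holds in conditional form. The article firmly plans treatment comparisons in strata that, for the stent and the guidewire, form after open-label allocation, and it neither standardises these measures nor stratifies by them. Intention-to-treat protects the comparison of all randomised patients, not of strata formed afterwards. Bonferroni limits chance findings, not selection.

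The size is 0 to about 5 percentage points under the assumed inputs, against an assumed overall effect of 15.8 − 4.4 = 11.4 points. The upper end needs a marked difference between the arms in who is stented. It would be too strong to call the tables meaningless in every case: they mislead only if use differs by arm in a way related to risk. The trial cannot fully verify that it does not, because not every determinant of risk is measured. The consequence is confined to secondary subgroup results.

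**What to change.** In {20b}, limit the subgroup list to variables whose value is fixed before randomisation. An anatomical feature such as a periampullary diverticulum still qualifies, even if it is first seen at the procedure. Remove the three measures from the list and report their use by arm as descriptive co-intervention data. That also shows readers whether use did differ.

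Optionally, add one clause to the general significance sentence in {20a}: except subgroup analyses, where the Bonferroni-adjusted threshold applies.

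The cost is wording only, with no extra patients or data and no change to the primary analysis or to N = 280. Three subgroup tables are lost. Recruitment is scheduled to run to 31 March 2027, so the change can be made before the analysis.
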